### Study setting and population

The MuCCUA trial is set in four communes of Huila and Cunene, two provinces of southern Angola. These provinces are predominantly rural with a combined total population of around 4.4 million (Huila population: 3 185 244 and Cunene population: 1 271 638).^38^ There are province-specific differences related to livelihoods. Huila has a higher agricultural productivity and lower food insecurity risk as compared with Cunene, mostly livestock activity, where the semiarid conditions and frequent droughts occasionally result in significant livestock loss, a key livelihood asset. Overall, the population is highly dependent on staple foods (primarily maize, millet and sorghum) and there is poor access to safe drinking water, hygiene and sanitation which may differ by commune also, due to the communes’ different geographical features. The socioeconomic status of clusters and households is expected to be homogeneous, as one of the clusters’ inclusion criteria was to experience extreme poverty. Different ethnic groups are present in the clusters but we do not expect diverse access to interventions according to ethnic origin as none of this groups are nomad. However, access to healthcare and other essential services differs in relation to the distance from the communities to the main settlements of each of the communes. There are remote communities where long distance, lack of transport and lack of trained health professionals and medicines make access to basic services inadequate.

The study participants are pregnant women confirmed by pregnancy test and over 16 years of age, and their newborn children. The target population of the interventions is the household in which the pregnant woman and their children live. In the case of having more than one pregnant woman within the household, all women who accept to participate will be included. We consider households to be the person or group of persons, with or without kinship relationships, who have been habitually living under the same roof for at least 6 months or less but with the intention of staying in the residence for the next 6 months and share food and/or other vital needs such as water, cooking and eating utensils and hygiene products. Informed cluster-level consent was sought from village leaders, sobas, to participate in the trial before randomisation. After acceptance to participate in the study through the informed consent, mothers and their children are followed up from the time of pregnancy at the time of recruitment until the child is 24 months old.

### Trial design

In the MuCCUA trial, a total of 36 purposively selected clusters (the selection of which is described below), with an estimated population of around 55 000, were randomised to the three trial arms with six clusters per arm in Huila province, and six clusters per arm in Cunene province. Two municipalities (admin 2) were selected per province (admin 1) with one commune (admin 3) per municipality (total two communes per province). In the province of Huila, the commune of Libongue (municipality of Chicomba) and the commune of Jamba Sede (municipality of Jamba) were selected. In the province of Cunene, the commune of Otchinjau (municipality of Cahama) and the commune of Mupa-Mukolongodjo (municipality of Cuvelai) were selected. The cluster unit is typically a village or neighbourhood and any nearby hamlets within each commune or, in the case of large neighbourhoods, a distinct part of it that is similar in population size to the unit. The randomisation, which took place in September 2022, was stratified by cluster.

The inclusion criteria for clusters were being considered as one of the municipalities prioritised by the FRESAN Programme and having a multidimensional poverty level 4 or 5 according to the Instituto Nacional de Estatística classification,^39^ not currently having or planned to have in operation other interventions offering monetary or nutritional transfers, acceptance by the municipal and traditional authorities, accessible in a 4×4 vehicle and having a reference health post with reference health personnel.

Recruitment and baseline survey started in October 2022 and will continue until March 2023. Implementation started at recruitment and is planned to end in November 2025. A total of 1440 pregnant women and their newborns, 480 in each arm, are enrolled. Primary efficacy analyses will be performed when the participant’s children have completed a total of 24 months of follow-up. A full description of the intervention design within the MuCCUA trial is described in detail elsewhere.^14^ A brief description of the interventions is presented in the following sections.

### MuCCUA interventions

#### Standard of care arm

This is the comparator arm. The communities allocated to this arm receive as intervention the standard of care alone, as described below.

The standard of care intervention comprises the recruitment of ADECOS and the implementation of a set of activities described in the National Development Plan of Angola^40^ and in the Multisectoral Strategic Plan on Nutrition,^41^ aligned with the WHO maternal and infant healthcare recommendations, following the National Policy of ADECOS. This intervention will be used as a comparator as it fulfils the criteria of acceptability, feasibility, relevance and uniformity required to be a good comparator in this type of studies.^42^ The standard of care activities can be grouped into two blocks:

Health promotion activities: including community interventions to promote adequate infant and young child feeding practices, identification of danger signs of malnutrition and referral to health posts and promotion of adequate hygiene, water and sanitation practices through sensitisation activities through the figure of ADECOS.Preventive pharmacological activities: including semiannual vitamin A supplementation for children 6–24 months old; semiannual deworming with albendazole for children from 12 months to 24 months of age and pregnant women from the second trimester; and malaria prophylaxis with sulfadoxine–pyrimethamine for pregnant women from 13th week of pregnancy through the health posts.

The standard of care is implemented in all the communities participating in the study, as detailed below.

#### Standard of care+nutritional supplementation

Communities allocated to this arm will receive the standard of care intervention plus nutritional supplementation to families with at least one pregnant woman enrolled. Nutritional supplementation will consist of SQ-LNS, a peanut-based ready-to-use home-fortification product to improve diet quality, for the pregnant women and their newborn children, and a complementary food ration for their families. The rations will be as follows: an individual ration of SQ-LNS for pregnant women Enov’Mum (1 sachet of 20 g daily) and Enov’Nutributter for children over 6 months (1 sachet of 20 g daily) produced and packaged in France by Nutriset. A complementary family food ration will comprise of a basket of locally produced staple foods that complements the usual diet (300 Kcal/person/day). The caloric distribution of the basket will be 45% of cereals (corn meal—carbohydrate), 30% of legumes (beans—vegetable protein) and 25% of oil (soybean oil—fat). In addition, 1 kg of iodised salt will be provided. The food basket is distributed in order to improve adherence to the SQ-LNS, contribute to greater participation and prevent intrafamily distribution of individual rations.

#### Standard of care+cash transfer

Communities allocated to this arm will receive the standard of care intervention plus an unconditional cash transfer to families with at least one pregnant woman enrolled. A total of 13 855 kwanzas/month (US$31.5, October 2022) will be delivered to households with four or more inhabitants. A total of 10 855 kwanzas/month (US$24.7, October 2022) will be delivered to households with three or fewer inhabitants. The minimum interprofessional salary in Angola at the time being is set at 35 000 kwanzas/month (US$79.5, October 2022). The amount will be directly delivered to study participants. The amounts of cash were selected based on the amount disbursed by the Kwenda Project, an Angolan Government programme funded by the World Bank aiming to fight poverty and to promote sustainable development in the communities with very poor households.

#### Measurement of health outcomes/effectiveness

The outcomes of the interventions will be assessed through repeated cross-sectional household surveys at baseline, at 6 months of pregnancy, 9 months of pregnancy, 3, 6, 12, 18 months of the newborn child, and endline at 24 months of newborn child.

The MuCCUA trial will test the effect of each of the experimental interventions (standard of care+nutritional supplementation, standard of care+cash transfer arms) relative to the control (standard of care arm). A detailed description of the trial outcomes is included in the trial protocol.^14^

#### Primary outcome

The MuCCUA trial primary outcome is prevalence of stunting as measured by height-for-age z-score (HAZ) or length-for-height z-score (LAZ) <−2 SD and mean HAZ or LAZ in children at 24 months of age in the provinces of Huila and Cunene.

The trial sample size was powered to measure an expected 13% reduction in stunting overall and to detect a difference in the non-inferiority margin of 10% between the proportions in the intervention groups (standard of care+nutritional supplementation and standard of care+cash transfer) and the comparison group (standard of care alone) post-intervention. We will conduct a cost-effectiveness analysis for cases of stunting averted if there is evidence of impact on the prevalence of stunting in children at 24 months at the 0.1 significance level or below. Cases averted by the two interventions relative to the control group for the outcome will be calculated at 24 months.

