### Mother and Child Chronic Undernutrition in Angola trial

The Crescer Project is an operational research programme on the prevention of chronic malnutrition in the southern Angolan provinces of Huila and Cunene. It is embedded in the FRESAN (Fortalecimento da Resiliência e da Segurança Alimentar e Nutricional em Angola) Programme, funded by the European Union (European Development Funds) to strengthen resilience and food and nutrition security in southern Angola. The Crescer Project implements the MuCCUA (Mother and Child Chronic Undernutrition in Angola) trial, a three-arm community-based cluster randomised controlled trial of non-inferiority which aims to evaluate the effectiveness and cost-effectiveness of a nutrition supplementation plus standard of care intervention and a cash transfer plus standard of care intervention compared with a standard of care alone intervention in preventing stunting in children at 24 months in Huila and Cunene. Pregnant women and their newborn children are target recipients of either arm: the comparator arm receives standard of care alone, the second arm receives standard of care plus nutrition supplementation with SQ-LNS and a family food ration, and the third arm receives standard of care plus unconditional cash transfers. Community and Health Development Agents (ADECOS) implement the interventions following Angolan Government protocols.^13^ The primary outcome is prevalence of stunting in children. The MuCCUA trial is described in detail elsewhere.^14^ The purpose of this protocol paper is to fully describe the methodology for the economic evaluation of the trial.

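### The non-inferiority label and 10% margin against standard of care contradict the aim of showing that two add-on interventions reduce stunting; the hypothesis should be superiority

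*Protocol article*

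**What the plan says.** The section Mother and Child Chronic Undernutrition in Angola trial describes "a three-arm community-based cluster randomised controlled trial of non-inferiority which aims to evaluate the effectiveness and cost-effectiveness". The Primary outcome section gives two sizing targets in one sentence: the trial was "powered to measure an expected 13% reduction in stunting overall", and it was also sized "to detect a difference in the non-inferiority margin of 10% between the proportions in the intervention groups" "and the comparison group (standard of care alone) post-intervention". The article does not say whether the 13% or the 10% is absolute or relative.

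The comparator is contained in both experimental arms. Under Standard of care arm: "The standard of care is implemented in all the communities participating in the study". The other two arms add either nutritional supplements with a family food ration, or monthly cash. Aim and objectives speaks of reducing stunting. Measurement of health outcomes/effectiveness says the trial "will test the effect of each of the experimental interventions" relative to control.

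The Primary outcome section allows the cost-effectiveness analysis only if there is evidence of impact on stunting at the 0.1 level or below. The Cost-effectiveness analysis section likewise asks for a statistically significant difference before ICERs are calculated.

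**The concern.** A non-inferiority margin suits a replacement treatment that offers some other advantage, for which a small loss of efficacy is acceptable. Here nothing is replaced. Each experimental arm delivers all of the comparator and then adds food or cash at extra cost. Showing that standard of care plus an add-on is not much worse than standard of care alone says nothing about whether the add-on prevents stunting. Read as absolute, a 10-point margin is compatible with no benefit, and with some harm. The article gives no reason for choosing non-inferiority.

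At stake is the trial's effectiveness conclusion. If the label were carried into the primary analysis, a null result could be reported as meeting the trial's objective. The unclear 13% adds a second problem: the two readings give very different power for the test that matters.

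**Working it through.** **Inputs from the article**
- 480 women per arm; 36 clusters over three arms, so 12 per arm and 480/12 = 40 per cluster (Trial design).
- Stunting prevalence 49.9% in Huila and 37.2% in Cunene (Burden of child undernutrition).
- 10% margin and 13% reduction (Primary outcome).

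**Assumptions**
- Control rate (49.9 + 37.2)/2 = 43.55%.
- Margin of 10 absolute points, tested at one-sided 0.025.
- Superiority tested at two-sided 0.05.
- ICC 0.01, 0.02 and 0.05; no loss to follow-up; 2 × 12 − 2 = 22 degrees of freedom, critical t = 2.074.

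**Can 480 per arm be reproduced?** No. The article does not give the power, trial alpha, ICC, loss or design control rate, so 480 can be neither confirmed nor refuted. Two benchmarks at 80% power, before clustering and loss:
- Superiority, 43.55% v 30.55%: n = [1.96√(2 × 0.3705 × 0.6295) + 0.842√(0.4355 × 0.5645 + 0.3055 × 0.6945)]² / 0.13² ≈ 216 per arm. Over control rates 37.2% to 49.9% the range is 197 to 227, so 480 leaves room for a design effect of 2.1 to 2.4. Since the design effect is 1 + 39 × ICC, that is an ICC of about 0.03 to 0.04.
- Non-inferiority with equal true rates: n = (1.96 + 0.842)² × 2 × 0.4355 × 0.5645 / 0.10² ≈ 386 per arm, range 367 to 393. This leaves a design effect of only 1.22 to 1.31, an ICC of about 0.006 to 0.008.

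So 480 sits more comfortably with superiority on 13 absolute points than with non-inferiority at equal rates.

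**Chance that an add-on with no effect meets the margin**

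SE = √[2 × 0.4355 × 0.5645 × (1 + 39 × ICC)/480]. The probability is that a noncentral t on 22 df, with noncentrality 0.10/SE, exceeds 2.074.

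| ICC | Design effect | SE | 0.10/SE | Declared non-inferior, no true effect | Same, stunting truly 5 points worse (0.05/SE) |
|---|---|---|---|---|---|
| 0.01 | 1.39 | 0.0377 | 2.65 | 72% | 24% |
| 0.02 | 1.78 | 0.0427 | 2.34 | 61% | 20% |
| 0.05 | 2.95 | 0.0550 | 1.82 | 41% | 14% |

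A normal approximation gives slightly higher figures (65% with no effect at ICC 0.02) and the same conclusion. A relative margin would be narrower (10% of 43.55% is about 4.4 points) and would give lower figures.

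**Power of a superiority test with the existing sample**

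SE uses each arm's own variance: √[(p₀(1 − p₀) + p₁(1 − p₁)) × (1 + 39 × ICC)/480]; noncentrality = difference/SE.

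| ICC | 13 points absolute (43.55% to 30.55%) | 13% relative (43.55% × 0.87 = 37.89%, 5.66 points) |
|---|---|---|
| 0.01 | 0.13/0.0364 = 3.57: 93% | 0.0566/0.0373 = 1.52: 31% |
| 0.02 | 0.13/0.0412 = 3.15: 85% | 0.0566/0.0422 = 1.34: 25% |
| 0.05 | 0.13/0.0531 = 2.45: 65% | 0.0566/0.0544 = 1.04: 17% |

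Using the control variance in both arms instead gives 91%, 83% and 62% for the absolute reading, a small difference.

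**The case against.** The best defence is that the defect lies in wording and not in the operative hypothesis. The sizing sentence opens with an expected reduction, the article says each arm's effect relative to control will be tested, and the Conclusion says the trial is powered to test differences between each arm and the comparison group. The sample size also fits superiority on 13 absolute points. This stands in part: it would be too strong to say that the trial was sized only as non-inferiority. It does not clear the text, which states the label in one section and the margin, with its comparator, in another. Nor can the label be meant for the comparison of the two active arms, since the margin sentence names standard of care alone and the Conclusion says the trial is not powered for the active-arm comparison.

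Two stronger readings are tempting, and the article does not support them:
- **That ICERs would rest on mere non-inferiority.** Both statements of the condition require evidence of a difference. With no true effect, a two-sided 0.1 test passes in the favourable direction only about 5% of the time.
- **That the trial will declare success on meeting the margin.** No decision rule for the primary test appears here, and the design is referred to a main trial protocol that is not shown. The 72%, 61% and 41% describe a rule assumed for illustration.

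It is also fair to say that an article may leave the ICC, alpha and loss to the full protocol. Their absence is not the point. The point is that the two figures the article does state conflict in purpose, and one of them has two readings.

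**Conclusion.** The concern holds as a contradiction in the stated hypothesis. The label and the margin against standard of care are at odds with the add-on design, the aim of reducing stunting, the expected 13% reduction, and the requirement of a demonstrated difference before any ICER is calculated. That part rests on the text alone and needs no assumption.

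The size of the consequence is conditional. The chance of about 41% to 72% that an ineffective add-on passes depends on the margin being the primary decision rule and on the assumed absolute scale, alpha, control rate, ICC and absence of loss. Whether the trial is adequately powered for the right question turns on the meaning of 13%: 65% to 93% power if absolute, 17% to 31% if relative, over the same ICCs.

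The expansion of LAZ in "height-for-age z-score (HAZ) or length-for-height z-score (LAZ" is a clerical slip. One might infer that the wrong index is being measured, but height-for-age stands beside it and stunting is named as the outcome, so it adds no weight.

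**What to change.** State superiority of each add-on arm over standard of care alone as the primary hypothesis, and remove the non-inferiority label and margin for that comparison in both sections. Say whether the 13% reduction is in percentage points or relative, and restate the power for that superiority test where the sample size is documented. As an editorial correction, expand LAZ as length-for-age.

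Sample size, conduct and data collection do not change. The cost is amended wording in the protocol and registry, and possibly a less favourable stated power, markedly so if 13% turns out to be relative. The hypothesis should be settled before the 24-month data are analysed.

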#### Cost-effectiveness analysis

Economic evaluation will be conducted as a within-trial analysis using the intention-to-treat results, and will be presented in terms of incremental cost-effectiveness ratios (ICERs), calculated as the difference in total costs of standard care only (or comparator) versus nutritional supplementation or cash transfer divided by the difference in mean effects of each intervention versus control. As mentioned previously, ICERs will be calculated in terms of cost per stunting case prevented among children at 24 months old if there is a statistically significant difference in the outcome between intervention study arms.

The ICER will be calculated to compare the additional costs per improved outcome achieved in interventions, including nutritional supplements or cash transfers, compared with the standard of care intervention. Where feasible, we will disaggregate costs for different time frames, including start-up versus recurrent costs.

Sensitivity analysis will be performed to determine the extent to which the results of the analysis might change given plausible variation in study parameters related to cost drivers and stunting rates. To obtain an estimate of how costs could vary, a range of costs will be calculated based on different scenarios such as local costs scenario, product price or coverage. Univariate and multivariate probabilistic sensitivity analyses will assess effect of the main cost drivers on the results.

All costs will be presented in 2022 Angola kwanzas and in US dollars (USD). We will use the average monthly exchange rate for the year of cost data collection to convert costs into USD. Any costs encountered in the past will be inflated using the local gross domestic product deflator of Angola, before converting to USD. In addition, some expenses will be in euros and we will use the average exchange rate for the year of cost data collection to convert costs into USD. All costs will be adjusted for inflation using the Angolan Consumer Price Index and will be converted to 2022 USD using the purchasing power parity conversion factor for Angola. Moreover, the costs will be discounted using a standard discount rate of 3%, as recommended by WHO-CHOICE^48^ and the Gates/IDSi Reference Case for Economic Evaluation.^49^

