## Conclusion

The findings of this trial will provide evidence on which intervention package can have the greatest impact on preventing stunting in children under 2 years in Angola and improve comparability with other contexts. Robust understanding of the costs and benefits of these types of nutrition strategies is critical for priority setting and to motivate ongoing donor investment and government partnership.

The cost estimation of the different arms of the trial will complement the effectiveness results to provide useful information to the Government of Angola and other policymakers on the most cost-effective and cost-efficient intervention to prevent stunting. Additionally, this study aims to gain understanding on the cost drivers, to promote inclusion of economic evaluations in other nutrition intervention studies and to improve comparability with other contexts.

One of the limitations of the MuCCUA trial is that it is only powered to test the differences between each of the intervention arms and the comparison group, but not to test the differences between the two intervention arms. The latter would require a larger sample size and resources beyond those available for the trial. However, the possibility of a direct comparison between the interventions will be explored. The protocol has all necessary ethical approvals and the findings of this study will be disseminated within academia and the wider policy sphere.

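### Cost per stunting case averted is reported only if the stunting effect is significant, although the abstract and the fourth objective promise it without condition

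*Protocol article*

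**What the plan says.** The condition appears twice. Under Primary outcome it reads "We will conduct a cost-effectiveness analysis for cases of stunting averted if there is evidence of impact on the prevalence of stunting in children", with the outcome taken at 24 months and the level set at 0.1. The comparison is with control: "Cases averted by the two interventions relative to the control group for the outcome will be calculated at 24 months". Under Cost-effectiveness analysis, the ICER is first defined as each intervention against standard of care. The text then refers back to the earlier rule and says that ICERs will be calculated "if there is a statistically significant difference in the outcome between intervention study arms". No significance level is given there.

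Two other places promise the same result with no condition: the Abstract (Methods and analysis) and the fourth specific objective under Aim and objectives.

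On power, the Conclusion says of the trial that "it is only powered to test the differences between each of the intervention arms and the comparison group". The Primary outcome section gives "an expected 13% reduction in stunting overall" as the effect for which the trial was sized, without saying whether this is absolute or relative.

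**The concern.** Cost-effectiveness is an estimation problem. A decision-maker needs the incremental cost, the incremental effect and the uncertainty around both, and a non-significant effect is part of that information. The rule has two consequences.

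- If the test is not significant, the fourth objective gets no answer. The article says that its findings will tell the Angolan Government which intervention is most cost-effective, and that answer would be missing although the data for it were collected.
- If the test is significant, the denominator of the ICER is an effect that has passed a filter. On average such an effect is too large, and when power is low this makes the intervention look cheaper per case averted than it is.

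The second statement of the rule is also loosely worded. It leaves the level to be inferred and does not say plainly which arms are compared. Neither statement says whether the rule applies to each intervention separately.

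**Working it through.** **The plan's own figure.** The article gives "A total of 1440 pregnant women and their newborns, 480 in each arm, are enrolled", but not the alpha, power, ICC or loss behind it, so 480 cannot be reproduced. It can be checked for plausibility. Take a control rate of 43.55%, the mean of 49.9% (Huila) and 37.2% (Cunene) in the Background, with two-sided 0.05 and 80% power. The usual two-proportion formula gives, before clustering:

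- 13 points absolute (43.55% to 30.55%): 216 per arm. Then 480/216 = 2.22 is the design effect that 480 allows. With 40 women per cluster this is an ICC of (2.22 − 1)/39 ≈ 0.031.
- 13% relative (0.13 × 43.55 = 5.7 points): 1182 per arm, far more than 480.

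The absolute reading therefore fits 480 per arm better.

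**Inputs for the gate.** From Trial design: 480 per arm and six clusters per arm in each of two provinces, so 12 clusters of 480/12 = 40. From Primary outcome: the 0.1 level. Assumed, because the article does not state them: control rate 43.55%, ICC 0.02 to 0.05, no loss, a two-sided test on 2 × 12 − 2 = 22 degrees of freedom, and passing counted only in favour of the intervention.

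**Formulas.** SE = √{[p₀(1−p₀) + p₁(1−p₁)] × (1 + 39 × ICC)/480}. The gate opens if estimate/SE > t(0.95, 22) = 1.717. The probability that it stays shut is Φ(1.717 − d/SE), where d is the true reduction. The mean estimate, and the mean of d/estimate, among trials that pass come from simulated normal draws. With incremental cost held fixed, d/estimate is the reported ICER as a fraction of the true one.

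**Example.** d = 0.13, ICC = 0.02. The design effect is 1 + 39 × 0.02 = 1.78. SE = √[(0.2458 + 0.2122) × 1.78/480] = 0.0412. The gate needs an estimate above 1.717 × 0.0412 = 0.071. Probability shut = Φ(1.717 − 3.155) ≈ 0.075.

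**Results, ICC 0.02 to 0.05:**

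| True reduction | Gate shut | Effect overstated, if reported | Mean ICER / true ICER |
|---|---|---|---|
| 13 points | 8–23% | 1.05–1.16 times | 1.02–0.92 |
| 10 points | 25–44% | 1.2–1.4 times | 0.91–0.77 |
| 5.7 points (13% relative) | 65–75% | 1.8–2.2 times | 0.59–0.47 |

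At 13 points and ICC 0.02 the mean ICER is slightly above the true one. The average of 1/estimate exceeds 1/(average estimate), and this outweighs the small selection effect.

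A wider range (ICC 0 to 0.05, loss 0 to 20%, normal critical value 1.645) gives the same picture. The gate is shut 0.5 to 24% of the time at 13 points, 6 to 44% at 10 points and 44 to 74% at 5.7 points, with overstatement of 1.00 to 1.17, 1.04 to 1.39 and 1.4 to 2.2 times.

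**After the fix.** With no gate the result is always reported, and its effect estimate is not selected on significance.

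**The case against.** The best defence is that the rule is prespecified, openly stated and set at a lenient level, and that it does little harm if the design assumption is right. Much of this stands. On the reading of 13% that fits 480 per arm, the gate opens about 87% of the time at an ICC of 0.031, and the mean ICER is then within about 1 to 2% of the true one. The article also sets "to detect a difference in the non-inferiority margin of 10% between the proportions in the intervention groups" and the comparison group as a difference between proportions, which again favours the absolute reading. A reader might infer that any reported ICER is biased in favour of the intervention. The figures at 13 points do not support that.

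A reader might also infer that the two statements of the rule contradict each other, the second requiring a difference between the two active arms, which the trial is not powered to test. The documents do not support that reading. The second statement refers back to the first, so the 0.1 level carries over. The sentence before it defines the ICER against standard of care. The Programme-related costs section counts standard of care among the intervention arms. This is loose wording to tidy.

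Nor does the whole economic evaluation disappear when the test fails. The first three objectives (programme costs, participant costs and cost per woman, child and household reached) carry no condition.

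Finally, probabilistic sensitivity analysis is planned, and the sensitivity analysis is to vary stunting rates. For cost per case averted, though, this can happen only once the gate has opened. The defence also needs a true effect near 13 points, and that effect is what the trial sets out to estimate.

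**Conclusion.** The concern holds in limited form. The gated text under Primary outcome and Cost-effectiveness analysis is inconsistent with the unconditional promise in the Abstract and the fourth objective. Following the gated text can leave that objective unanswered.

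Non-reporting is the firmer harm: about 8 to 23% of the time for each comparison even at a true 13 points, and more at smaller effects. The bias is conditional. It is minor at 13 points, moderate at 10 and large only if the true effect is nearer 5.7 points, where the mean reported ICER is about half the true one (0.47 to 0.59).

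All these sizes rest on the assumed control rate, ICC, absence of loss and two-sided test. That the rule exists, and that the objective is stated without it, rests on the text alone.

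**What to change.** Delete the significance condition in both sections. For each intervention versus standard of care, report incremental cost, incremental cases averted and their joint uncertainty whatever the p-value. A bootstrap that resamples clusters is one suitable method. Add incremental net benefit or acceptability curves, so that the result stays defined when the effect is near zero and the ratio is unstable. The choice among these tools can be left to the analysis plan.

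Under Cost-effectiveness analysis, replace the wording about a difference between intervention arms with each intervention versus standard of care. This matches Measurement of health outcomes/effectiveness, Primary outcome and the Conclusion.

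The change needs no new data, only revised wording and a modest amount of extra analysis. The price is that a wide or unfavourable cost-effectiveness result may have to be published.
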